# LIST OF ABBREVIATIONS

| Abbreviation or Term^1^ | Definition/Explanation |
| --- | --- |
| AE | Adverse event |
| ALT | Alanine aminotransferase |
| ANCOVA | Analysis of covariance |
| ANOVA | Analysis of variance |
| APTT | Activated partial thromboplastin time |
| AST | Aspartate aminotransferase |
| AV | Atrioventricular |
| β-HCG | Beta-human chorionic gonadotropin |
| BID | Twice daily |
| BLQ | Below limit of quantification |
| BMI | Body mass index |
| BP | Blood pressure |
| BUN | Blood urea nitrogen |
| Ca^++^ | Calcium |
| CBC | Complete blood count |
| CFR | Code of Federal Regulations |
| CHF | Congestive heart failure |
| CI | Confidence interval |
| Cl- | Chloride |
| CL_cr_ | Creatinine clearance |
| C_max_ | Maximum observed concentration |
| C_min_ | Trough observed concentration |
| CNS | Central nervous system |
| CR | Complete response |
| CRF | Case report form |
| CT | Computed tomography |
| CTCAE | Common Toxicity Criteria for Adverse Events |
| CV | Coefficient of variation |
| CYP | Cytochrome P450 |
| D/C | Discontinue |
| DEA | Drug Enforcement Administration |
| ECOG | Eastern Cooperative Oncology Group |
| eCRF | Electronic case report form |
| DLT | Dose Limiting Toxicity |
| ECG | Electrocardiogram |
| Eg | Exempli Gratia (for example) |
| FACS | Fluorescence-Activated Cell Sorting |
| FDA | Food and Drug Administration |
| FDG-PET | Fluorodeoxyglucose (FDG)-positron emission tomography (PET) |
| GCP | Good Clinical Practice |
| GFR | Glomerular filtration rate |
| GGT | Gamma-glutamyltransferase |
| GLP | Good laboratory practice |
| HBsAg | Hepatitis B surface antigen |
| HBV | Hepatitis B virus |
| HCO_3_^-^ | Bicarbonate |
| HCV | Hepatitis C virus |
| HIV | Human immunodeficiency virus |
| HR | Heart rate |
| hr | Hour or hours |
| IC_50_ | Half maximal inhibitory concentration |
| i.e. | Id est (that is) |
| IEC | Independent ethics committee |
| IND | Investigational New Drug |
| INR | International normalized ratio |
| IRB | Institutional review board |
| IU | International unit |
| IV | Intravenous, intravenously |
| LDH | Lactate dehydrogenase |
| LLQ | The lower limit of quantitation |
| MedDRA | Medical Dictionary for Drug Regulatory Activities |
| MRI | Magnetic resonance imaging |
| MRSD | The maximum recommended starting dose |
| MTD | Maximum tolerated dose |
| NOAEL | No-observed-adverse-effect level |
| NOEL | No-observed-effect-level |
| PD | Pharmacodynamic(s) |
| PFS | Progression-Free Survival |
| PK | Pharmacokinetic(s) |
| PO | Per os (administered by mouth) |
| PR | Partial response |
| PT | Prothrombin time |
| PTT | Partial thromboplastin time |
| QC | Quality control |
| RBC | Red blood cell |
| QD | Once-daily |
| QTc | QT interval corrected |
| QTcF | QT interval corrected using Fredericia equation |
| SAE | Serious adverse event |
| SD | Standard deviation or stable disease |
| T_1/2_ | Terminal elimination half-life |
| T_3_ | Triiodothyronine |
| T_4_ | Thyroxine |
| T_max_ | Time of maximum observed concentration |
| TID | Three times daily |
| TSH | Thyroid-stimulating hormone |
| ULN | The upper limit of normal |
| ULQ | The upper limit of quantitation |
| UV | Ultraviolet |
| WBC | White blood cell |
| WOCBP | Women of childbearing potential |
| WONCBP | Women of nonchildbearing potential |

^1^ All of these abbreviations may or may not be used in the protocol.

# STUDY SUMMARY

| Title | PAPR: Psilocybin-assisted psychotherapy (PAP) + Mindfulness-based Stress Reduction (MBSR) for front-line healthcare provider COVID-related depression and burnout. |
| --- | --- |
| Short Title | PAPR |
| Protocol Identifiers (IRB – internal) |  |
| IND number | 163040 |
| Phase | Pilot |
| Design | Open-label, pilot trial. |
| Study Duration | 1.0 years |
| Study Center(s) | This is a single-center trial to be conducted at Huntsman Mental Health Institute |
| Objectives | **Primary Objectives**   - To assess the safety and tolerability of psilocybin in the study population. - To assess the feasibility to recruit, consent, and enroll healthcare providers in a study of psilocybin-assisted therapy + MBSR vs. MBSR and for those participants to remain in the study until completion. - To assess the effect that psilocybin-assisted therapy has on depression symptoms in healthcare providers with burnout as measured by the QIDS-SR-16.   **Secondary Objectives**   - To assess the changes in rates of provider burnout as measured by the Maslach Burnout Inventory for Medical Professionals (MBI-HSS (MP)) both in terms of rates of meeting criteria for burnout as well as mean reduction in score on the MBI. - To assess the long-term effect that psilocybin-assisted therapy and MBSR have on depression and anxiety symptoms in the study population. - To assess the effect psilocybin therapy and MBSR have on symptoms of post-traumatic stress syndrome. - To assess the effect psilocybin therapy and MBSR have on participant reported quality of life. - To assess the effect psilocybin therapy and MBSR have on participant reported feelings of connectedeness to self, other, and world.   **Exploratory Objectives**   - To assess the effect psilocybin therapy, in conjunction with an MBSR curriculum, has on state and trait mindfulness measures. - To assess participant-reported psilocybin experience on the day of medication administration and to assess the relationship between reported experience and depression and burnout response. - To use the Storyline Health AI platform to develop a model for precision research on psychedelic-assisted therapies and healthcare provider burnout and to better characterize predictors of response to mindfulness training and psilocybin therapy utilizing the Storyline Integrative Assessment tool. |
| Number of Subjects | 25 |
| Diagnosis and Main Eligibility Criteria | **Key Inclusion Criteria:**   - Male or female healthcare providers aged ≥ 25 years old. - Participants must be physicians or nurses with at least 1 month of frontline clinical experience during the COVID-19 pandemic. - Screening MBI-HSS (MP) score that meets our working definition of burnout (emotional exhaustion subscale ≥ 27) and a ‘high’ score on one other subscale (either depersonalization ≥ 13 or personal accomplishment ≤ 21). - PHQ-9 depression screen ≥ 10. - Not taking regularly scheduled medications to treat depression and/or anxiety, including benzodiazepines, for at least 4 weeks prior to initiation of the study.   **Key Exclusion Criteria:**   - Prior systemic antidepressants, anti-psychotic, or anxiolytic medication within four weeks prior to psilocybin administration. - Personal history or immediate family members with schizophrenia, bipolar affective disorder, delusional disorder, schizoaffective disorder, psychosis, dementia, or other psychotic spectrum illness. - Currently meeting DSM-5 criteria for Dissociative Disorder, or other psychiatric conditions judged to be incompatible with the establishment of rapport or safe exposure to psilocybin. - Currently meeting DSM-5 criteria for Cluster B Personality Disorder). - Current or history within the last two years of meeting DSM-5 criteria of substance use disorder (excluding caffeine and nicotine). |
| Study Product, Dose, Route, Regimen | Psilocybin 25 mg PO |
| Duration of administration | One-time administration |
| Reference therapy | MBSR |
| Statistical Methodology | Feasibility will be assessed by the ability to recruit, consent, and enroll 24 patients in the trial, and for at least 16/24 patients to remain in the study until completion.  The key secondary analysis of QIDS-SR-16 and MBI-HSS(MP) will use mixed-effects models with fixed effects for time (enrollment, 2 weeks post psilocybin), and a random intercept term. The outcome variables are the estimated change from baseline to 2 weeks post psilocybin from these models. |

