# STUDY DESIGN

## Description

Recruitment will target physicians or nurses with at least 1 month of frontline clinical experience during the COVID pandemic who meet DSM-5 criteria for a depressive disorder, including adjustment disorder with depressed mood.

Participants that meet eligibility criteria and have a screening MBI-HSS (MP) score that meets our working definition of burnout (emotional exhaustion subscale ≥ 27) and a ‘high’ score on one other subscale (either depersonalization ≥ 13 or personal accomplishment ≤ 21) as well as a PHQ-9 depression screen ≥ 10 will be offered enrollment and following a consenting process will be randomized to either MBSR or MBSR + PAP with 12 participants per group. PHQ-9 and MBI-HSS questionnaires may be administered prior to consenting to assess eligibility. Consenting will be completed in person with paper or electronic consenting forms. The MBSR group will complete an 8-week MBSR curriculum (online) through the University of Utah Resiliency Center led by [name], LCSW which includes a weekly 2.5-hour sessions over Zoom for 8 weeks and an 8 hour in-person retreat between weeks 6 and 7. If capacity within the University of Utah MBSR groups limits enrollment and feasibility we will incorporate the MBSR programs through Intermountain as well as Davis Behavioral Health. We will run subjects through the MBSR curriculum in flexible numbers concurrently until a total of 12 have completed this arm. The MBSR + PAP group will complete this same curriculum, however will substitute an 8-hour group-format psilocybin-assisted therapy session (with 25 mg psilocybin capsule) with 1:1 therapist to participant ratio instead of the MBSR retreat day. Each participant will have an assigned individual therapist present for the duration of the psilocybin dosing session. A lead therapist ([name] PhD) will also be present for all study sessions including the psilocybin dosing day and there will be at least one lead study monitor present for the duration of the psilocybin dosing day ([name] MD or [name] MD). The psilocybin intervention will be completed in groups of 2-6 individuals per cohort. Additionally, the MBSR + PAP group will have 3, 90-minute group preparatory sessions prior to the psilocybin session and 3 subsequent 90-minute integration sessions. The first integration session will occur 1-2 days following the psilocybin session. A communal music track will be played during the PAP session. After the enrollment and treatment of the first four patients, accrual will be placed on hold to ensure participant safety. If stopping rules are not met, we will continue with enrollment.

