## Number of Patients

This study will enroll a total of 24 patients with 12 patients in each study arm.

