## Study Duration

Study therapy will be a total of 9 weeks duration (with 8-week MBSR curriculum) and patients will be followed for 6 months (180 days) after completion of the study intervention. There will be a total of two groups of 12 subjects per study arm. Total duration for the study will be approximately one year.

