### Statistical Power

### Power is based on the efficacy of MBSR+PAP vs. MBSR alone in reducing symptoms of depression. A meta-analysis examining the effects of psilocybin on depressive symptoms reported an effect size of Cohen’s d=1.29. Previous meta-analyses of MBSR indicate modest to moderate effect sizes for depressive symptom reduction (Cohen’s d= 0.3 to 0.4). We conducted simulation-based power calculations for the linear mixed-effects model. Assuming a **large between group effect size (Cohen’s d = 1.0)**, alpha=0.05, and a **moderate-to-high intra-class correlation (ICC = 0.5)**reflecting the repeated measures design, the estimated power to detect a **treatment group × time interaction** in the LMM was approximately **81%**. Given the pilot nature of this study, the primary goal was to estimate effect sizes and assess feasibility to inform future larger-scale trials.

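### The Study Summary states 25 subjects, but the feasibility criterion, Section 4.1 and Section 4.2 all give 24, and Section 4.4 is worded so that it conflicts with 12 per arm

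*Protocol*

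**What the plan says.** The protocol states its planned size in five places.

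- Study Summary, number of subjects: "Number of Subjects | 25".
- Study Summary, statistical methodology: the feasibility aim is to "enroll 24 patients in the trial, and for at least 16/24 patients to remain in the study until completion".
- Section 4.1 (Description): participants are "randomized to either MBSR or MBSR + PAP with 12 participants per group". The same section says the MBSR curriculum will be run "in flexible numbers concurrently until a total of 12 have completed this arm".
- Section 4.2 (Number of Patients): "This study will enroll a total of 24 patients with 12 patients in each study arm".
- Section 4.4 (Study Duration): "There will be a total of two groups of 12 subjects per study arm".

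Section 1.1 makes enrollment, retention and completion part of the first primary objective. The only numerical benchmark for them is the one in the Study Summary.

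**The concern.** The summary row and the feasibility criterion stand in the same table and differ by one participant. Section 4.4 adds a phrase that can be multiplied out to something other than 12 per arm. In most trials a one-patient slip in a synopsis would pass as a typing error. Here the ability to reach the planned enrollment is itself a primary outcome, so the planned number is part of what the trial will be judged on. A reader who takes the size from the summary row would say that a trial enrolling 24 fell one short, while the feasibility criterion would say that it met its target.

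Section 4.1 adds a related problem. Counting completers in the MBSR arm is a different accrual rule from enrolling 12 in that arm, and the protocol does not say which one ends recruitment.

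**Working it through.** **Step 1. The plan's own total.** Sections 4.1 and 4.2 give two arms of 12: 2 × 12 = 24. This agrees with the enrollment target in the feasibility criterion, so 24 is reproduced.

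**Step 2. The statements side by side.**

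| Place | Stated | Implied total | Agrees with 24? |
|---|---|---|---|
| Study Summary, number of subjects | 25 | 25 | No |
| Study Summary, feasibility criterion | enroll 24, retain 16/24 | 24 | Yes |
| Section 4.1 | 12 per group | 2 × 12 = 24 | Yes |
| Section 4.2 | 24, with 12 per arm | 24 | Yes |
| Section 4.4 | two groups of 12, per arm | 24 if one group is one arm; 2 × 12 × 2 = 48 if multiplied out | Depends on the reading |

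An odd total such as 25 could only be 12 + 13, which no section describes.

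**Step 3. Effect on the retention benchmark.** As written, the benchmark is 16/24 = 66.7%. The same count over 25 would be 16/25 = 64.0%, a difference of 2.7 percentage points. The protocol writes the denominator as 24, so this shows only how little one participant matters.

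**Step 4. Effect on power.** Inputs from the Statistical Power section: between-group effect d = 1.0, alpha 0.05, ICC 0.5. The plan does not say whether the test is one- or two-sided; two-sided is assumed. On a scale with unit SD, the change from baseline has SD √(2 × (1 − 0.5)) = 1. By the normal approximation, with n per arm, power = Φ(d√(n/2) − 1.96).

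- n = 12 (total 24): Φ(2.449 − 1.96) = 68.8%
- n = 12.5 (total 25, taken as an average): Φ(2.500 − 1.96) = 70.5%

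The difference is 1.7 points. With the t distribution the two values are 64.9% and 66.8%. With adjustment for baseline (SD √0.75 = 0.866, normal approximation) they are 80.7% and 82.3%. Whatever the method, the 25th participant is worth about 2 points.

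**Step 5. What the completer rule could do.** If the MBSR arm runs until 12 complete, the expected number enrolled in it is about 12 divided by the completion rate. The plan assumes no rate for this trial, so a range is shown:

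- 100% completion: 12
- 82% (the rate cited from a prior study under Sample size determination): 12/0.82 = 14.6, about 15
- 66.7% (the 16/24 benchmark): 12/0.667 = 18

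Unless completion is perfect, this rule and 12 enrolled per arm cannot both hold.

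**The case against.** The strongest reply is that the protocol already settles the matter. The feasibility criterion gives the enrollment target and the retention denominator in one sentence, Section 4.2 is the section meant to govern the number of patients, and Section 4.1 agrees. The 25 enters no analysis and no decision rule. All of this stands, and it limits the point to an inconsistency that needs correcting.

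Three stronger readings are tempting, and the document supports none of them.

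- A reader might infer that the feasibility denominator is left open. It is not: it is written as 16/24.
- A reader might infer from Section 4.4 that 48 is a further planned size. That comes from one clumsy sentence under the duration heading and is contradicted by the feasibility criterion and by Sections 4.1 and 4.2. The psilocybin sessions are run in cohorts of at most 5 or 6 (Sections 6.1 and 9.2), so a group of 12 sensibly means an arm. The stated power of about 81% does not point to 48 either: by the calculation in Step 4, 24 per arm would give 93.4%, or 92.4% with the t distribution.
- A reader might turn 16/24 into a two-thirds standard and ask what count it would require at 25. The protocol sets a count of 16 out of 24. Its two-thirds rule, in Section 12.1, concerns session attendance for the per-protocol set.

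It can also be said that the completer wording in Section 4.1 merely describes how participants pass through the course. That may be what was meant, but as written it names completion as the point at which the arm is full.

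**Conclusion.** The point holds as an internal contradiction in the stated sample size. The summary's 25 is the outlier against three statements of 24, and Section 4.4 needs rewording because its literal sense does not fit 12 per arm. The size of the problem is one participant: about 2 points of power under the plan's own effect size and ICC (two-sided test assumed), and no change to a retention rule that is fixed at 16/24. It deserves correction because enrollment is a primary outcome. It does not threaten the design.

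The completer rule in Section 4.1 is the part that could affect conduct, since it can carry enrollment in the MBSR arm past 12. How far depends on a completion rate that the plan does not assume.

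**What to change.** 1. In the Study Summary, change the number of subjects from 25 to 24.
2. In Section 4.4, reword the sentence as *two arms of 12 subjects each*.
3. Keep the retention benchmark at 16/24.
4. In Section 4.1, reconcile the sentence that runs the MBSR arm until 12 have completed it with the 12 enrolled per arm in Section 4.2, stating whether accrual stops on participants enrolled or on participants completing. If completers are meant, Section 4.2 and the feasibility criterion must be brought into line with that choice.

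Items 1 and 2 are corrections of wording, and item 3 changes nothing. Item 4 needs one decision and a sentence. If accrual stops at 12 enrolled per arm, no analysis or threshold changes.

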**Schema**

[figure not shown]

# OBJECTIVES

## Primary Objectives

### Determine the acceptability, feasibility, and safety of psilocybin-assisted therapy (PAP) plus Mindfulness-Based Stress Reduction (MBSR) for front-line healthcare worker burnout.

*Primary Endpoint:* Acceptability of each modality will be determined by ease of enrollment and retention. Feasibility will be measured by the number of enrollees who successfully complete each modality in both study arms. Safety will be measured through the monitoring of adverse events (AEs) utilizing the CTCAE (NCI Common Terminology Criteria for Adverse Events Version 5.0), suicidal ideation utilizing the Columbia Suicide Severity Rating Scale (C-SSRS), administration of the Challenging Experiences Questionnaire (ChEQ), direct participant qualitative reports, and clinician observation.

### Assess the preliminary efficacy of MBSR+PAP vs MBSR alone in reducing symptoms of depression (as measured by the QIDS-SR-16).

*Primary Endpoint:* Efficacy will be assessed through mean reduction in QIDS-SR-16 scores at 2-weeks post intervention with between-group comparison. To understand longitudinal effects, we will gather data to 6 months post intervention for both arms. Participants will be screened for eligibility with the PHQ-9 with a cut-off score of ≥ 10 required for enrollment and participants must meet DSM-5 criteria for a depressive disorder (including adjustment disorder with depressed mood).

*Primary Endpoint:* The change in depression scores as measured by the QIDS-SR-16 from enrollment to 26 weeks post-completion of the intervention (MBSR curriculum).

## Secondary Objectives

### To assess the effect of MBSR vs. MBSR+PAP has on the participant-reported symptoms of burnout (as measured by the MBI-HSS(MP)).

*Secondary Endpoint:* The change in mean MBI-HSS(MP) scores from baseline to 2 weeks post intervention with between-group comparison.

*Secondary Endpoint:* The change in mean MBI-HSS(MP) scores from baseline to 6 months post-completion of MBSR intervention.

### To assess the effect of MBSR vs. MBSR+PAP on symptoms of demoralization using the Demoralization II Scale (16 item)

*Secondary Endpoint:* The change in the Demoralization II Scale scores from baseline to two weeks post-completion of MBSR intervention.

### To assess the effect MBSR vs. MBSR +PAP has on symptoms of post-traumatic stress as assessed by the PCL-5 PTSD checklist

*Secondary Endpoint:* The change in PCL-5 scale scores from baseline to two weeks post-completion of MBSR intervention.

### To assess the effect MBSR vs. MBSR + PAP has on measures of connectedness to self, other, and world.

*Secondary Endpoint:* The change in score on the Watts’ Connectedness Scale (WCS) scale from baseline to two weeks post-­completion of the MBSR intervention.

## Exploratory Objectives

### To capture and explore behavioral data markers using the Storyline Health AI platform that may relate to other study outcomes and which may inform future research utilizing the Storyline Health Integrative Assessment tool.

We will be utilizing *Storyline Health* to track user questionnaires, experiences and other study data. This is a recently developed system that will allow us to track a variety of behavioral data points previously difficult to track including micro-expressions, pupillometry, voice tone, cadence and prosody, among other markers. Storyline Health is a platform that allows scalable, remote, and objective profiling of human cognition, expression, and behavior using a video-enabled smartphone. Storyline enables researchers to create clinical and behavioral assessments and care pathways, deploy them at scale to user smartphones and capture video responses that are securely stored in the cloud. The researcher then launches the Storyline AI pipeline, which extracts over 20,000 different measures of human facial, speech, and vocal patterns in each video, such as sub-second facial micro-expressions, facial blood flow patterns, word choice, sentiment, and vocal micro-tremors. The de-identified data is stored in storyARC and storyTIME files for download, analysis and sharing. Using Storyline, precise biomarkers and predictive models of illness, disease subtypes, drug responses and outcomes can be discovered, validated and then delivered instantly to providers and patients through **Storyline Telehealth**. The **Storyline Library** is an “App-like store” that makes proven assessments, models and care pathways available to providers. Therefore, Storyline seamlessly integrates clinical research with care delivery at scale, enabling rapid translation of biomarkers and algorithms.

*Tertiary Endpoint:*

- We will deploy the Storyline Integrative Assessment (see Appendix 1) to narrow in on specific feature selection in small cohorts of patients with deep AI phenotyping to identify behavioral phenotype predictors of burnout, which is heterogeneously characterized. This will be administered to both study arms at baseline, at the primary outcome point (2 weeks post intervention on both study arms), and at 6 months post intervention.

*Tertiary Endpoint:*

- We will deploy Storyline technology to narrow in on specific feature selection using deep AI phenotyping to identify phenotypical predictors of treatment response to both MBSR as well as MBSR+PAP to better characterize factors that predict response to both interventions, which may inform future research. This will be administered to both study arms at baseline, at the primary outcome point (2 weeks post intervention on both study arms), and at 6 months post intervention.

